### Objectives

The primary objective of the trial was to evaluate the effectiveness of the implementation of clinical pathways for hospital treatment of heart failure among a sample of Italian hospitals. Our hypothesis was that the clinical pathways should be more effective than usual care in treating patients admitted in hospital for heart failure and that the clinical pathways should reduce patients' mortality during the stay and that they should improve patients' outcomes at discharge.

Secondary objectives were to estimate the efficiency and the appropriateness of the use of the resources associated with the intervention and its effects on other relevant outcomes.

The third objective was to define a statistical model able to predict in-hospital death and unscheduled re-admission.

A follow up study to evaluate the effectiveness of the intervention after three years from baseline was described in a separate protocol.

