### Study evaluations

The primary outcome measure is in-hospital mortality. We will also analyze the impact of the clinical pathways comparing the length and the appropriateness of the stay, the rate of unscheduled readmissions, the customers' satisfaction and the costs treating the patients with the pathways and with the current practice along all the observation period. The quality of the care will be assessed by monitoring the use of diagnostic and therapeutic procedures during hospital stay and by the use of key quality indicators at discharge, as reported in previous studies [18-22]. The list of process and outcome indicators is reported in Table 1.

**Table 1 T1:** The indicator set.

**Indicator (measure)**	**Typology**	**Criterion met/expected change**	**Measure**
In hospital mortality	Outcome	Differences in rates	%
Length of hospital stay	Outcome	Differences in mean values	days
Appropriateness of the stay (with Appropriateness Evaluation Protocol – AEP)	Outcome	Differences in rates	%
Costs of the stay (with Activity Based Costing – ABC)	Outcome	Differences in mean values	€ (euro)
Rate of unscheduled readmissions (within 31 days)	Outcome	Differences in rates	%
Patients' satisfaction (survey with 16 items questionnaire)	Outcome	Differences in mean values	score (1–10)
Diagnostic procedures during hospital stay	Process	Differences in rates	%
*Echocardiography*			
*Trans-oesophageal echocardiography*			
*Electrocardiography*			
*Chest x-rays*			
*Oximetry*			
*Weight monitoring*			
*Diuresis monitoring*			
Medical treatment during hospital stay	Process	Differences in rates	%
*Inotropes*			
*ACE-inhibitors*			
*Beta-blockers*			
*Diuretics*			
*Nitrates*			
*Other vasodilators*			
*Heparin*			
*Oral anticoagulants*			
*Anti-platelets agents*			
Left ventricular function (LVF) assessment rate at discharge (or planned for after discharge)	Process	Given to all patients	%
Rehabilitation rate at discharge (or planned for after discharge)	Process	Given to all patients	%
Advice/counseling rate for smoking cessation at discharge	Process	Given to all patients (current smokers)	%
Written instructions rate at discharge (activity level, diet, discharge medications, follow up, weight monitoring and what to do if symptoms worsen)	Process	Given to all patients	%
ACE-inhibitor rate at discharge (without contraindications, with LVF < 40%)	Process	Given to all patients	%

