### Study sample

The sample included all the patients treated by the hospitals during the experimental period with a principal diagnosis of heart failure (all ICD-9CM codes included in 428.xx code). We calculated the sample size needed to detect a statistical difference in the mortality rate. Since in Italy the in-hospital mortality rates range from 5% to 17%, we expected that clinical pathways succeeded to control mortality to 5% to be clinically relevant [23-25]. Based on this goal a sample size of 424 patients (212 in each group) was required for the study to have 80% power at the 5% significance level (two-sided). The sample size calculation was performed according to standard criteria for cluster randomized trials. We adjusted the sample size using an inflation factor of 1.51 to account for the cluster randomization: 7 clusters per trial arm, cluster size of 30 patients, ICC of 0.018 [26-29].

At baseline we verified the comparability of the two groups at the admission measuring patients' age, sex, co-morbidities, risk factors and symptoms severity (Table 2). Patients with a current AMI or unstable angina were excluded from the study.

**Table 2 T2:** Characteristics of 429 Hospital Patients in the Clinical Pathway and Usual Care Study Groups (demographics, risk factors and disease severity at admission).

**Variable**	**Clinical pathway **(n = 214)	**Usual Care **(n = 215)	**p value**
Male gender	102	110	0.50
Mean age in years (SD)	81.7 (8.3)	79.6 (8.5)	0.011
*Admitted from*			
General practitioner	106	109	0.77
Home	108	106	
*Severity at admission*			
NYHA II	16	15	
NYHA III	117	114	0.87
NYHA IV	81	86	
*Co morbidities*			
Hypertension	154	161	0.58
COPD	52	58	0.58
Diabetes	41	38	0.71
Smoking	34	31	0.68

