### Data analysis

Data were prospectively collected by local staff both in intervention and in control groups (physician and nurses who were trained in two pre-study educational events). We did not use incentives for the local staff.

The analysis will be performed by the research team. In addition to common descriptive statistics (Fisher exact and Kruskal Wallis test for categorical and continuous variables, respectively), that will be performed at the cluster level, the differences in the rate of in-hospital deaths and unscheduled admissions across groups and according to each variable under study will be evaluated using random-effects logistic regression, thus accounting for the clustering effect [30-33]. Variables will be included if significant at the 0.10 level (backward approach), with the exception of age which will be forced to entry. The presence of multicollinearity, interaction and higher power terms will be assessed to check final model validity. Patients who died during the study will be excluded from the regression model evaluating unscheduled readmissions because they could not be re-admitted.

Statistical significance will be defined as a two-sided p-value < 0.05. All analyses will be intention-to-treat and will be carried out using STATA statistical software, version 8.2 (Stata Corporation, College Station, Texas, 2003).

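### The selection rule for the mortality regression protects only age, so the study arm can be dropped from the model meant to carry the primary comparison

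*Protocol article*

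**What the plan says.** All references are to the protocol article.

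- Study evaluations: "The primary outcome measure is in-hospital mortality". Table 1 gives its criterion as a difference in rates, in per cent.
- Data analysis: the two binary outcomes, death in hospital and unscheduled readmission, are compared as follows: "across groups and according to each variable under study will be evaluated using random-effects logistic regression, thus accounting for the clustering effect".
- The next sentence gives the retention rule: "Variables will be included if significant at the 0.10 level (backward approach), with the exception of age which will be forced to entry".
- It is followed by: "The presence of multicollinearity, interaction and higher power terms will be assessed to check final model validity".
- The Fisher and Kruskal-Wallis tests in the same section are presented as descriptive statistics. No other model-based comparison of the arms on mortality is described.
- Objectives: "The third objective was to define a statistical model able to predict in-hospital death and unscheduled re-admission". Data analysis does not limit the backward rule to this objective.

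**The concern.** The group comparison on deaths is placed in a regression, and the sentence directly after it makes staying in a regression depend on p < 0.10, with one named exception. The arm is not that exception. A rule of this kind suits a prediction model. Applied to the randomised contrast, it makes reporting of the model estimate depend on its own p-value.

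Two things are at stake. When the effect is modest or absent, the model that accounts for clustering may contain no arm term, and so give no adjusted odds ratio or confidence interval for the primary outcome. When a modest effect does pass the 0.10 screen, it passes because the estimate came out large, so the reported odds ratio is too far from 1.

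This is a rule that the article states, not a detail left to a fuller document.

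**Working it through.** **Inputs from Study sample.** 212 patients per arm, 7 clusters of 30 per arm, ICC 0.018, inflation factor 1.51, pathway mortality 5%. Usual-care mortality is not fixed; only 5% to 17% is given. From Data analysis: retention at 0.10, age forced.

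**The plan's own figure first.** An assumed 15% vs 5% fits the stated size. With mean rate 0.10:

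n = [1.960·√(2·0.10·0.90) + 0.842·√(0.15·0.85 + 0.05·0.95)]² / 0.10² = (0.8315 + 0.3521)² / 0.01 = 140.1 per arm; 140.1 × 1.51 = 211.5, so 212.

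17% vs 5% gives 106 × 1.51, about 161 per arm (185 with continuity correction), which does not match. So 15% is a plausible basis for the calculation, but it is an inference.

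**Chance that the arm is deleted.** Effective size per arm is 212/1.51 = 140.4. With d = p0 − p1, s0 = √(2·p̄·q̄/140.4) and s1 = √((p0q0 + p1q1)/140.4), the arm is retained with probability Φ((d − 1.645·s0)/s1).

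- 15% vs 5%: (0.10 − 1.645·0.0358)/0.0353 = 1.16; retained 88%, deleted 12%.
- 11% vs 5% (11% is the midpoint of 5% and 17%): (0.06 − 1.645·0.0324)/0.0322 = 0.21; retained 58%, deleted 42%.

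| Usual care vs pathway | Deleted, formula | Deleted, clustered simulations (arm only) | Deleted, backward elimination simulated without clustering |
|---|---|---|---|
| 17% vs 5% | 6% | – | – |
| 15% vs 5% | 12% | 10% and 12% | 3% |
| 11% vs 5% | 42% | 38% and 43% | 26% |
| 15% vs 8% | 42% | – | 29% |
| 15% vs 10% | 65% | 66% | 52% and 57% |
| no effect | 90% | 89% and 90% | 89% and 91% |

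The clustered simulations used 7 + 7 beta-binomial clusters of 30 with ICC 0.018. One fitted a random-effects logistic model (1,500 trials per scenario); the other used a Wald test adjusted for the design effect (40,000 trials). The last column ran actual backward elimination with age forced and Table 2-type covariates. It is lower because it omits the cluster inflation.

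**Exaggeration when retained.** The true odds ratio at 11% vs 5% is (0.05/0.95)/(0.11/0.89) = 0.43. The median odds ratio among trials that keep the arm is 0.32 (0.31 in the second clustered simulation). At 15% vs 10% it is 0.44 against 0.63. In the unclustered backward elimination at 15% vs 8%, the mean log odds ratio is −0.86 among retained trials, against −0.69 for a fixed age-plus-arm model. At 15% vs 5% the distortion is small: −1.27 against −1.21.

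**If the arm is always kept.** Unclustered simulations with arm and age forced and the other covariates selected at 0.10 gave:

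- No effect: rejection at 0.05 of 5.0% with selection against 4.1% without in one set, and 6.2% both ways in another. Interval coverage in the first set was 95.0%.
- 15% vs 5%: coverage 96.4%; mean log odds ratio −1.25 with selection against −1.22 without.

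Even when the arm could be deleted, and deletion counted as no rejection, null rejection was 5.3% against 5.7% for the fixed model.

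**The case against.** The strongest reply is that the authors never meant to drop the arm. The sentence before the rule names the groups separately from the variables under study, so the rule can be read as screening covariates, or as building the third objective's prediction model. That reading is reasonable. But the text names one exception, and it is age; nothing confines the rule to covariates or to prediction. Nor does the article say outright that a single model serves both aims, so the point rests on the missing separation and not on a declared merger.

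Three stronger readings are tempting, and the documents do not support them.

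- *No treatment effect would be reported at all.* Table 1 still provides the crude difference in mortality rates. What would be lost is the clustering-adjusted estimate and its interval.
- *Even with the arm kept, covariate selection invalidates the p-value and interval.* The simulations show no material type I error inflation, loss of coverage or bias. What stands is that the adjustment set is not fixed in advance.
- *There are too few deaths for the arm comparison.* At 15% vs 5%, 31.8 + 10.6 = 42.4 deaths are expected, about 4 for each of 10 parameters (the Table 2 variables plus arm). That bears on the starting model for prediction and does not show that the arm test fails. The interaction and higher-power terms are described as a check on the final model, not as a search for effects.

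It is also fair to say that 11% vs 5% is not a scenario in the article, and that the deletion rates are largely one minus power at the 0.10 level. They still measure what the rule does.

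**Conclusion.** The concern holds in this form. As written, the rule leaves the arm unprotected in the regression for the primary outcome. Deletion would occur in about 10–12% of trials at 15% vs 5%, about 40% at 11% vs 5% and about 90% under no effect. A modest effect that is retained is overstated (median odds ratio about 0.32 against 0.43 at 11% vs 5%).

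These sizes assume the stated ICC and cluster numbers and an assumed usual-care rate. They apply only if the rule is followed literally. If the arm is kept by intention, the residual defect is minor: an adjustment set chosen from the outcome data, without demonstrated damage to the test. Because the literal rule decides whether the primary model estimate exists, the wording should be corrected before analysis; the section still describes the analyses in the future tense.

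**What to change.** In Data analysis, state that:

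1. study arm, age and a short prespecified set of baseline covariates (for example sex and NYHA class, both already in Table 2) are forced, without selection, into the random-effects logistic models for in-hospital mortality and for unscheduled readmission;
2. the arm odds ratio and its 95% confidence interval are reported whatever the p-value;
3. backward selection and the examination of interaction and higher-power terms apply only to the separate prediction model of the third objective, which is not used to judge the pathway.

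The cost is wording only: no new data, patients or clusters. How the prediction model is penalised or validated is a matter of preference and is not part of this point.

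### The between-arm readmission comparison drops everyone who died, so it is conditional on survival, and its exclusion rule is worded more widely than its reason supports

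*Protocol article*

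**What the plan says.** All references are to the protocol article.

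- **Data analysis.** Random-effects logistic regression is to evaluate "the differences in the rate of in-hospital deaths and unscheduled admissions across groups". The readmission model is thus used to compare the arms.
- **Data analysis, same paragraph.** "Patients who died during the study will be excluded from the regression model evaluating unscheduled readmissions because they could not be re-admitted".
- **Data analysis, next paragraph.** "All analyses will be intention-to-treat". That sentence names no exception.
- **Study evaluations.** "The primary outcome measure is in-hospital mortality". Table 1 lists unscheduled readmission as a separate outcome with a 31-day window. The only death outcome in the table is in-hospital mortality.
- **Objectives.** The hypothesis includes that "clinical pathways should reduce patients' mortality during the stay". The third objective is a statistical model to predict in-hospital death and unscheduled readmission.
- **Study sample.** Italian in-hospital mortality is given as 5% to 17%, and "we expected that clinical pathways succeeded to control mortality to 5% to be clinically relevant". No single usual-care rate is stated, and no readmission rate is given anywhere.

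**The concern.** The exclusion depends on an event after randomisation, and that event is the one the trial expects to differ by arm. If the pathway works as hypothesised, some patients who would have died under usual care leave hospital alive in the pathway arm and enter its readmission denominator. Their counterparts in usual care are dropped. If those patients are frailer than other survivors, the pathway arm shows more readmissions even where the pathway changes nobody's readmission risk. A true benefit on the primary outcome would then appear as a disadvantage on a secondary one.

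The wording adds a second problem. The reason given, that the dead could not be readmitted, is true of deaths during the index stay. It is not true of a patient who went home, was readmitted within 31 days and died afterwards. Taken as written, the rule covers that patient too and deletes an observed readmission.

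**Working it through.** **1. The plan's own figure, used to find a working mortality rate.** The article gives 212 patients per arm, 80% power, two-sided 5%, a pathway rate of 5% and an inflation factor of 1.51. The usual-care rate is not stated. Using the pooled two-proportion formula without continuity correction:

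- 15% vs 5%: 141 × 1.51 = 212.9 per arm, which agrees with 212.
- 16% vs 5%: 121 × 1.51 = 182.7. With continuity correction, 139 × 1.51 = 209.9, which is also close.
- 17% vs 5%: 106 × 1.51 = 160.1 (184.2 with continuity correction), which does not agree.

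I use 15% below. It is back-solved and is not a planning value that the article states.

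**2. How many patients the rule removes, counting in-hospital deaths only.**

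- Usual care: 212 × 0.15 = 31.8.
- Pathway: 212 × 0.05 = 10.6.

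The excluded share is three times larger in usual care if the primary hypothesis is true.

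**3. Illustration of the bias.** Assumptions:

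- 85% of patients survive under either care.
- 10% survive only under the pathway, and 5% die under either.
- Nobody dies because of the pathway.
- The pathway has no effect on anyone's readmission risk.

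Let r0 be the readmission risk in the 85% and r1 the risk in the 10%. Both are assumed.

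- Usual care, survivors only: r0.
- Pathway, survivors only: (0.85 × r0 + 0.10 × r1) / 0.95.
- In-hospital death or readmission, all patients: usual care 0.15 + 0.85 × r0; pathway 0.05 + 0.85 × r0 + 0.10 × r1.

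Example with r0 = 15% and r1 = 40%: pathway readmission is (0.1275 + 0.0400) / 0.95 = 17.6% against 15.0%. The odds ratio is (0.1763/0.8237) / (0.15/0.85) = 1.21.

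| r0 | r1 | Survivors only, usual care | Survivors only, pathway | Odds ratio | Death or readmission, usual care | Death or readmission, pathway |
|---|---|---|---|---|---|---|
| 15% | 15% | 15.0% | 15.0% | 1.00 | 27.8% | 19.3% |
| 15% | 30% | 15.0% | 16.6% | 1.13 | 27.8% | 20.8% |
| 15% | 40% | 15.0% | 17.6% | 1.21 | 27.8% | 21.8% |
| 15% | 50% | 15.0% | 18.7% | 1.30 | 27.8% | 22.8% |
| 20% | 30% | 20.0% | 21.1% | 1.07 | 32.0% | 25.0% |
| 20% | 50% | 20.0% | 23.2% | 1.21 | 32.0% | 27.0% |

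Over r0 of 15–20% and r1 of 30–50%, the spurious odds ratio runs from 1.07 to 1.30. At the top of the stated mortality range (17% vs 5%) the same grid gives 1.08 to 1.37. If saved patients have the same risk as other survivors, it is 1.00.

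**4. Bias against sampling error.** There would be about 212 × 0.95 = 201 pathway and 212 × 0.85 = 180 usual-care survivors. In the worked example the variance of the log odds ratio is 1/(201 × 0.176 × 0.824) + 1/(180 × 0.15 × 0.85) ≈ 0.078. Multiplied by 1.51 this is about 0.117, a standard error of about 0.34. The bias, ln 1.21 = 0.19, is therefore about 0.56 standard errors.

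**The case against.** Much can be said for the plan.

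- **Readmission is undefined for someone never discharged.** A rate among patients discharged alive is a legitimate descriptive measure. It also suits the third objective, where restricting a prediction model to patients at risk is ordinary practice. This stands. The difficulty is only with the other use of the model, the comparison across groups.
- **The exclusion is disclosed.** A reader might infer a flat contradiction of intention-to-treat. The article does not support going that far: the exclusion and its reason are stated just before the intention-to-treat sentence, and nothing suggests that survivors leave their hospital's randomised arm. What remains is that the sentence claims all analyses and should name the exception.
- **The rule may mean only index-stay deaths.** In-hospital mortality is the only death outcome in the article, and the reason given fits that reading. A reader might infer that fatal readmissions will certainly go uncounted, or that the rule hides harm shifted to after discharge. Neither is established. The first depends on the literal reading. As to the second, the article does not show that deaths after discharge are collected, and the primary outcome would not capture them whatever this rule says.
- **The bias may be small or nil.** Every readmission rate above is assumed, the illustrated bias is well under one standard error, and covariates kept in the model may absorb part of it. This stands as a limit on size. It does not restore a randomised comparison.
- **In-hospital mortality is reported by arm.** A reader will see both components, though not combined per patient.

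**Conclusion.** The point holds as a moderate one. The between-arm readmission comparison is conditional on survival, which is the primary outcome and is hypothesised to differ by arm, so it is not an intention-to-treat contrast. As worded, the rule also reaches patients for whom its stated reason is false.

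The likely direction is against the pathway, provided that patients whose deaths are averted are more prone to readmission than other survivors. The size cannot be fixed from the article. The 1.07–1.30 range rests on a back-solved 15% mortality and on assumed readmission risks. The all-patient outcome favours the pathway in every row of the table because it keeps the averted deaths in view.

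A reader might take this as a fault that must be corrected before the trial can be interpreted. The article does not support that: readmission is one of several secondary outcomes, the primary mortality analysis is untouched, and the illustrated bias alone would not be expected to overturn a conclusion.

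**What to change.** 1. Limit the exclusion to deaths during the index stay. Keep patients who die after discharge in the denominator, and count those readmitted within 31 days who then die as readmitted.
2. Label that result as conditional on discharge alive, and name it as an exception in the intention-to-treat sentence.
3. For the comparison of arms, add a random-effects logistic model of in-hospital death or unscheduled readmission within 31 days, in all patients of all randomised hospitals, with both components tabulated by arm. Include deaths outside hospital after discharge only if they are collected.

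The cost is a few sentences and one extra model, using two outcomes already listed in Table 1. The drawback is that the composite mixes two outcomes of different weight, which is why the components must be shown separately. The survivors-only model can stay for the prediction objective.

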### Ethics

The project was exempt from ethical clearance according to the Italian Ministry of Health law number (ex art. 12bis D.lgs 229/99). Moreover the aim of the study is to improve quality of care through clinical pathways and thus should not imply any risk for the patients affected by the study. It is difficult to imagine that our intervention based on better evidences and appropriate use of technologies and drugs could worsen the quality of care when compared to usual care. So according to other experiences dealing with clinical pathways or implementation of evidence based guidelines in practice we think that a Committee of Research Ethic would not consider it necessary to submit the protocol for approval [34,35].

